
#### Secondary outcome measure—examination of the children’s ears

The other part of the baseline data collection is examination of the children’s ears. The secondary outcome measure is a reduction in the prevalence of CSOM and other abnormalities of the tympanic membrane in the intervention group compared to the control group. We will also offer a health check to all of the children. It is likely that this will be well-received as it is rare for a medical doctor to leave the district capital. The field team leader, an experienced Australian General Practitioner, will examine the children’s ears and take a digital image of their eardrums with a Welch Allyn Digital Macroview Otoscope, if possible, for later verification with an Ear Nose and Throat specialist blinded to allocation. All images will be identified by number only and submitted to the Ear Nose and Throat specialist who will be the final arbiter of diagnosis. CSOM will be diagnosed according to WHO Guidelines with aural discharge of more than two weeks [1]. There is considerable variation internationally about the duration of discharge needed to diagnose CSOM, so children with discharge for longer than six weeks and three months will be documented and analysed separately [38]. Height, weight, middle upper arm circumference, vision, heart and skin checks will also be performed. Weight will be measured to nearest 100 g with Seca 876 scales, height will be measured to nearest 1 mm with Seca 217 mobile height measurement and length to nearest 1 mm with Seca 210 mobile measurement mat. Vision checks will use Revised Sheridan Gardiner Test, which is suitable for illiterate children. Research assistants will be trained in accurate use of equipment and recording of data by the field team leader using WHO Training Course on Child Growth Assessment (2008) [39]. The field team leader will perform skin, heart and ear examinations. Children with medical issues will be referred to health posts or the local hospital, as appropriate. Any child with a current ear infection will also be offered treatment or referral to local health services. There is no specialist ear service in Jumla It would not be ethical to deny treatment to any child. Results of the examination will be recorded on a paper that will also record the ID number of their mother or grandmother**.**

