### Study design

Our study uses a cluster randomised trial design and is profoundly informed by our previous qualitative study (unpublished), consisting of in-depth interviews with women in Jumla, Nepal. Existing women’s self-help groups will be the unit of randomisation, or cluster. This is a suitable method for an intervention that takes place at the group level and is commonly used in community-based interventions [18, 19, 22–24]. Stratification will be done to avoid sampling bias, as power is better maintained than with matching. The 56 existing groups will be stratified into according to Village Development Committee and the remoteness of their location and distance to the road. Although all of these groups are in a remote location, distance to the road determines accessibility of health and other services. Following stratification, a random sample of 30 groups will be chosen for the study. Randomisation will be done using a computer generated random number sequence in Australia, by a member of the team (HW) not involved in data collection. The selection will then be communicated to the field team leader by internet or telephone. We will seek individual informed consent from each participant woman. After baseline data collection, groups will be randomly allocated to the intervention group and to the control group, stratified by geography. Randomisation will again be performed by a team member in Australia using a computer generated random number sequence and communicated to the field team leader by internet or telephone. The intervention will then be implemented over three consecutive regular monthly meetings of the self-help groups. International Nepal Fellowship is the only non-government organisation working directly with women in the two Village Development Committees, so it is unlikely that any co-interventions might contaminate the study. Women in Jumla are not generally mobile. A small number of women do migrate to India to work with their husbands and these women could be lost to follow-up but the numbers are likely to be very small. In the 2011 census, only 341 women in the entire district of Jumla were absent from their their homes [25]. Follow-up assessment at 12 months, repeating the women’s questionnaire and examination of the children’s ears will complete the study. Ethical approval has been granted by Human Research Ethics Committee, University of New South Wales (Ref# 13361) and Nepal Health Research Council (Ref # 1434).

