### Content of the intervention

The intervention is community-based and participatory and it will not be possible for participants to be blinded after allocation. The design of the intervention is greatly dependent upon the interviews from our exploratory qualitative study. Those interviews with women revealed that they enjoy meeting and learning together in their groups and that they had a strong preference for visual and interactive presentations. Three sessions will take place within the existing regular monthly meeting of the women’s self-help group meeting in the intervention groups. The intervention is based on the WHO *Primary Ear Care Training Programme*, which has been widely adopted in India and other low resource settings. The basic level of the programme aims to educate parents, carers and community health workers about ear infections, their recognition, risk factors, prevention, risk of hearing loss and appropriate care-seeking [21]. Session 1 and Session 2 will be facilitated by the field team leader. Session 3 will be completed by the usual group facilitator. Recap of previous sessions is a normal part of their group meetings. The content of each session is standardised. Attendance at each session will be recorded and a sensitivity analysis performed.

#### Session 1

The first session is an interactive education session using drama and pictures. We have developed a new resource using local photographs based on the *WHO Primary Ear Care Training Programme—Basic Level.* The first of four components shows the importance of the ear and the sense of hearing—demonstrating the usefulness of being able to hear every day noises such as a baby crying, conversation, dogs barking and, for children, hearing in the busy classroom. The second component is identifying signs and symptoms of ear infections including ear pain, discharge, pulling at ears, fever and irritability. The third section details the transmission of ear infections via coughing, sneezing, touching and dirty water. The final section examines ear care, not putting anything in the ear, such as sticks, oil or any or substance, encouraging appropriate care seeking at the local health post and explaining about the medications that will be provided there.

#### Session 2

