### Outcome measures

#### Primary outcome measure—the questionnaire

The survey instrument for women in the intervention and control groups is a questionnaire. The primary outcome measure is a 25 % difference in knowledge, attitude and practices, regarding ear disease in their children, of women in the intervention group compared to the control group. There are demographic questions such as age, number of children, maternal education, food security, usual health practices followed by questions about knowledge, attitude and practice regarding ear health, hearing, ear disease and health care seeking. The questionnaire uses already validated questions from the Demographic Health Survey (DHS) and Multiple Indicator Cluster Survey (MICS) performed recently in Nepal and is informed by a similar survey conducted in South India [32, 36, 37]. Other questions have been inspired by the *Primary Ear and Hearing Care Training Resource* and the literature on health care engagement [21]. The knowledge section asks the question ‘what do women know about ear infections in their children’, what are the local causes, treatments and complications. The attitude section queries ‘what do women think about ear infections’, is there a low level of ‘threat perception’, are there cultural barriers to seeking care, is there a perception of poor quality care or that ear infections are incurable. Finally, the practice section inquires what they do about them, whom they consult, if anyone, what would help them seek care and whether they know what care is available. The questionnaire has been pre-tested in Australia with a small adjustment made to a single question. The duration in English with educated mothers is 10 mins. Pretesting with village women on the terai (plains) did not reveal any difficulties with the questionnaire. We then undertook a formal pilot study of 20 village women in Jumla, attending INF clinics in Jumla Bazaar, to check for length, understanding and clarity. For these uneducated and illiterate women, the survey was too long and several questions incomprehensible to them. The questionnaire was edited appropriately and five questions removed from the demographic section. The new questionnaire was clear and can be completed in 10-15 mins. The questionnaires will be completed on paper in Nepali by the research assistants trained by the field team leader. Training will take place over two days in Jumla bazaar. A number of interviews will be observed by the field team leader to ensure quality control and all forms will be reviewed regularly to ensure correct completion by assistants. Baseline assessment will be performed prior to allocation into intervention and control groups to avoid bias. Group attendance and financial records are strictly kept at each meeting so it is not possible for an outsider to attend a group meeting unobserved. It is possible that there could be contamination of the control group by an intervention group member offering advice. This is not very likely as extended family mostly live side by side, meaning that grandmothers, aunties and mothers, who might share childcare and advice, are in the same group, or cluster. There are few sources of health information for these mainly illiterate women in this remote region. Followup assessment will be performed 12 months after baseline assessment. The trained research assistants performing followup assessment will be blinded to allocation.

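### Blinding of the 12-month CSOM diagnosis is not secured: the only named ear examiner teaches the intervention, and the blinded image reading cannot show the discharge duration that defines CSOM

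*Protocol article*

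**What the plan says.** **Who knows the allocation.** Under Study design, the result of randomisation is "communicated to the field team leader by internet or telephone".

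**Who teaches.** Under Content of the intervention: "Session 1 and Session 2 will be facilitated by the field team leader". The usual group facilitator leads the third session.

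**Who examines.** Under the secondary outcome measure: "The field team leader will perform skin, heart and ear examinations". The leader also takes the eardrum images. Study design adds: "Follow-up assessment at 12 months, repeating the women’s questionnaire and examination of the children’s ears will complete the study". No other ear examiner is named.

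**The safeguard.** Eardrums are photographed "if possible, for later verification with an Ear Nose and Throat specialist blinded to allocation". Images carry a number only, and the specialist has the last word on diagnosis.

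**The case definition.** "CSOM will be diagnosed according to WHO Guidelines with aural discharge of more than two weeks". Durations beyond six weeks and beyond three months are also documented and analysed separately.

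**The questionnaire.** For the primary outcome: "The trained research assistants performing followup assessment will be blinded to allocation". The same section says: "A number of interviews will be observed by the field team leader to ensure quality control and all forms will be reviewed regularly".

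**The concern.** The leader cannot be masked, because the leader receives the allocation and stands in front of the intervention groups. If that person also examines the children at 12 months, protection of the CSOM outcome rests on the specialist. The specialist's reading covers only children with an image and only what an image can show. Duration of discharge is history, and it decides whether a discharging ear counts as CSOM. The article mentions no history going to the specialist and no blinded person collecting it.

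Uneven probing or recording of duration, or uneven success in obtaining images, could create a difference in CSOM prevalence where none exists, or hide a real one. Ascertainment of this kind cannot be repaired in the analysis.

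The primary outcome carries a smaller risk. If the leader's observation of interviews extends to follow-up, the women's own teacher could be present at a knowledge interview. That could prompt taught answers and show the assistant which arm the group is in.

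**Working it through.** The plan gives no figure on this point, so the check has two parts.

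**1. Roles traced through the protocol article**

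| Step | What the text gives | Blinded? |
|---|---|---|
| Allocation received | Field team leader (Study design) | No |
| Sessions 1 and 2 | Field team leader (Content of the intervention) | No |
| Ear examination and imaging | Field team leader; no other examiner named (secondary outcome) | At baseline yes, since allocation comes later; at 12 months no, if the leader examines |
| Reading of images | Specialist, where an image exists | Yes |
| Discharge duration | Recorder not stated; no route to the specialist stated | Not secured |
| Questionnaire at follow-up | Research assistants (primary outcome) | Stated as yes |

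The blinded step reaches eardrum abnormalities that show on an available image. It does not reach duration, nor any child without an image.

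**2. How much misclassification would matter (illustration only)**

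Inputs:
- Prevalence 7.6%, the Nepal survey figure in the Background. It is for ages 5 to 13, while the trial takes children aged 12 and under.
- Children per arm: assumed 600 (40 per group × 15 groups), with 300 (20 per group) as the alternative. The article gives about 600 women in total, so about 300 per arm, and no number of children.
- ICC: 0 and 0.01 are assumed. 0.03 and 0.05 are the values in the Sample size calculation, chosen there for the questionnaire.
- No true effect; all error is under-recording in the intervention arm.

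Expected cases per arm: 0.076 × 600 = 45.6, about 46; 0.076 × 300 = 22.8, about 23.

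Design effect: DE = 1 + (m − 1) × ICC. For m = 40 and ICC 0.01, 1 + 39 × 0.01 = 1.39.

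Test: z = (p1 − p2) / √[2 p(1 − p) × DE / n], where p is the pooled proportion.

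Example, 46 v 29 of 600 with DE = 1: the difference is 17/600 = 0.02833; pooled p = 75/1200 = 0.0625; SE = √(2 × 0.0625 × 0.9375 / 600) = 0.01398; z = 2.03.

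Smallest number of missed cases giving z ≥ 1.96:

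| Children per arm | ICC | DE | Cases compared | Missed | Share | z |
|---|---|---|---|---|---|---|
| 600 | 0 | 1.00 | 46 v 29 | 17 of 46 | 37% | 2.03 |
| 600 | 0.01 | 1.39 | 46 v 26 | 20 of 46 | 43% | 2.06 |
| 600 | 0.03 | 2.17 | 46 v 22 | 24 of 46 | 52% | 2.03 |
| 600 | 0.05 | 2.95 | 46 v 19 | 27 of 46 | 59% | 2.00 |
| 300 | 0 | 1.00 | 23 v 11 | 12 of 23 | 52% | 2.12 |
| 300 | 0.03 | 1.57 | 23 v 9 | 14 of 23 | 61% | 2.03 |
| 300 | 0.05 | 1.95 | 23 v 8 | 15 of 23 | 65% | 1.98 |

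These are the shares needed for misclassification alone to reach significance. Smaller shares still distort the test. With 300 to 600 children per arm and ICC 0 to 0.05, missing 20% of intervention-arm cases raises the chance of p<0.05 under no effect from 5% to about 8–18%; missing 30% raises it to about 13–36%.

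**The case against.** - **Blinding of the primary outcome is stated.** A reader might infer that neither outcome is protected. The text does not support that. Research assistants administer the questionnaire and are said to be blinded at follow-up. The leader observes only some interviews, and the text does not say whether this is at baseline, at follow-up or both. Nor does it say who reviews the forms, so that task cannot be assigned to the leader as fact. This stands: the questionnaire's blinding is at risk, not lost.
- **Part of the secondary outcome is protected.** It also covers other eardrum abnormalities. Where an image exists, the blinded reading deals with those. This stands.
- **Some links are inferred.** The section on ear examination opens with baseline, when nobody knew the allocation. That the leader examines at 12 months follows from the repeat examination and the absence of any other examiner. Who takes the discharge history, and whether the specialist receives it, is not stated; nothing says it is withheld. A full protocol might settle these points. This limits how firmly the point can be put. It does not remove it, because the article presents the blinded specialist as the safeguard for a diagnosis that an image alone cannot make.
- **The illustration needs large, one-sided error.** At the ICCs the protocol itself uses, more than half of the intervention-arm cases would have to be missed for bias alone to reach significance. This stands, and it is one reason for not rating the point higher.

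**Conclusion.** The concern holds for CSOM at follow-up: blinded ascertainment is not secured by the arrangements described. It rests on three stated facts (the leader's knowledge of allocation, the leader's teaching role, and a case definition based on duration) and on the strong inference that the leader examines again at 12 months. It does not extend to eardrum abnormalities visible on an available image. For the questionnaire, it amounts to a risk that the text leaves open.

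The size cannot be fixed from the document. Under the stated assumptions, misclassification alone would need to affect 37% to 59% of intervention-arm cases with 600 children per arm, and 52% to 65% with 300, to give p<0.05. Smaller error inflates the false-positive rate without reaching that point.

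This should be fixed, mainly for the secondary outcome. The article reports that data collection has begun, so the change needs to be settled before the 12-month assessment.

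**What to change.** At the 12-month assessment:

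1. A blinded research assistant asks fixed questions on presence and duration of ear discharge before the ear examination, and records the answers on a form the leader does not alter.
2. The specialist, blind to arm, assigns the CSOM diagnosis used in the analysis from that history plus the image where there is one, and from the history alone where there is none. The leader's own diagnosis serves the child's care only.
3. The share of children without an image is reported by arm, with a sensitivity analysis for them.
4. The leader does not observe follow-up interviews.

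**Cost:** one short form and slightly longer visits, using staff already in place.

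**What remains:** mothers cannot be blinded, and those in the intervention arm have been taught to recognise discharge, so their reports may still differ. The leader still takes the images, so uneven imaging is made visible by item 3 but not prevented.

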### Harms

Confidentiality will be strictly kept. Completed questionnaires, children’s data sheets and digital images will be identified by number only. The paper forms will be kept in a locked box in the field. Consent forms will be kept in the same box. All paper data will subsequently be stored in the security protected locked filing cabinet in the basement storage of the School of Public Health and Community Medicine, University of New South Wales. Electronic data will be kept on a password protected computer. This research has a very low possibility of causing harm. Women could become distressed while discussing their children’s health. In the unlikely event that followup is needed the field team leader will organise this with local health services. Any children found to have medical conditions will be referred to local health services. The authors are the co-ordinating committee for this research and take responsibility for co-ordination and data management. The endpoint of the research is predetermined and the risk for harm is minimal.

### Sample size calculation

The sample size is calculated on the primary outcome. Using data extracted from questions in the previous qualitative study, sample size for an unclustered study with a 5 % two sided Type 1 error and 80 % power to detect a 25 % difference in mean questionnaire score, would be 114 women in each arm. Both Daly et al. in USA and Srikanth et al. in India found a very low level of knowledge about causes and risk factors for otitis media in mothers of young children [37, 40]. We anticipate a similarly low level in Jumla, and hypothesise that a 25 % increase would be modest and achievable. The cluster sizes are set at the size of the women’s groups which is around 20 women. To adjust for clustering, it is necessary either to establish an approximate intra-cluster correlation coefficient (ICC) or ρ, which measures the similarity of individual responses within clusters, in order to calculate the design effect (the number by which an individual trial must be multiplied to adjust for clustering) or to calculate the between cluster variability, k. These values vary and any estimate can only be approximate. Other studies on neonatal mortality in women’s groups in Nepal have found a very low ICC of 0.00644 [24]. Tielsch et al. [41] calculated a design effect of 1.23 with their study of supplements to prevent malnutrition in children. Mullany et al. [22] used a design effect of 2.0 for their study looking for a 25 % reduction in omphalitis in newborns in rural Nepal. Slightly further afield in Bangladesh, Aboud et al. [23] calculated an ICC of 0.03 for a responsive feeding and stimulation intervention to clusters of rural women and children. Pagel et al. [42] reviewed ICC for interventions around perinatal outcomes in low resource countries and found universally low ICC for maternal and neonatal mortality but higher ICC for other interventions such as skilled birth attendance. For example, in India and Bangladesh skilled birth attendance ranged from ICC 0.02-0.04. The Design Effect (DEff) is the number by which the sample size for an individual randomised controlled trial must be multiplied to give the equivalent power to a cluster randomised trial. The Design Effect also considers the number of individuals in each cluster *– m.* Using the equation DEff = 1 + (*m*-1) ρ, assuming ρ = 0.03, would give a DEff = 1.6, or 182 women per arm. Using the safe equation DEff = 1 + (m-1) ρ, assuming ρ = 0.05, would give a DEff = 1.95, or 223 women per arm. This would translate into 11 clusters per arm. To account for stratifying, we have added a conservative extra two clusters per arm, which would make 13 clusters per arm. To enable robust cluster analysis a minimum of 15 clusters is ideal. This will provide a generous total sample of approximately 600 women in 30 clusters, 15 in the intervention and 15 in the control arm.

### Statistical analysis

Analysis will be by intention-to-treat, all study participants will be included in the analysis, even if lost to follow-up. Analysis will be adjusted for clustering. Every effort will be made to have complete data but missing data will not be ignored in the analysis. Data will be checked and cleaned before being entered into Statistical Package for the Social Sciences. At baseline a comparison profile of both intervention and control groups will be provided. The primary and secondary outcomes - difference in mean questionnaire score and prevalence of CSOM - will be compared between the two groups. Data will be analysed at both individual and cluster level. Cluster level analysis is very robust and, with 15 clusters in each arm, individual level analysis, adjusted for clustering ought also to be very robust. For the primary outcome, a summary measure, the mean score of the questionnaire, will be calculated and then the intervention and control group compared for significance with a *t*-test at the cluster level. For individual level analysis, we plan to use mixed effects linear regression, which adjusts for the effect of clustering. The secondary outcome is a proportion, so we plan to analyse individual level data using logistic regression random effects model, using quadrature checks, which also adjusts for clustering. Since the age range is quite broad we will consider each standard age grouping in our analysis: under one year, under five years, and five years and over. We will also analyse duration of ear discharge as this is strongly correlated with prognosis. Covariates including socioeconomic status, education, caste, geography and number of household members will be considered.

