### Study population

The participants are members of the existing women’s self-help groups and their household children age 12 and under. All members of the study groups will be invited by International Nepal Fellowship staff to participate. In this setting it is likely that all members will agree to participate as the burden on them is very slight. Women who live in a household with a child aged 12 and under will be included in the survey since rural Nepalis mostly live in extended family groups and mothers-in-law are important decision-makers for child health [33–35]. CSOM is a chronic condition and occurs at all ages, with a peak in early childhood. The age of 12 has been chosen as the upper limit as most young children continue to live with their families and attend local schools. Older children are increasingly moving to the district capital for the later years of high school, which would make followup assessment difficult.

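### The promise to analyse everyone, even those lost to follow-up, is not met by the analyses as described; define intention-to-treat by allocated group and model baseline and 12-month scores together

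*Protocol article*

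**What the plan says.** The Statistical analysis section of the protocol article adopts intention-to-treat and explains it as "all study participants will be included in the analysis, even if lost to follow-up". It adds: "Every effort will be made to have complete data but missing data will not be ignored in the analysis". No technique for missing data is named.

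The same section lists three outcome analyses:

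- Primary outcome, cluster level: "the mean score of the questionnaire, will be calculated and then the intervention and control group compared for significance with a" t-test.
- Primary outcome, individual level: "we plan to use mixed effects linear regression, which adjusts for the effect of clustering".
- Secondary outcome (CSOM prevalence): a "logistic regression random effects model, using quadrature checks, which also adjusts for clustering".

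The covariates to be considered are socioeconomic status, education, caste, geography and household size. The baseline questionnaire score is not among them.

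On timing, the questionnaire section states: "Followup assessment will be performed 12 months after baseline assessment". There is no assessment in between. On losses, the Study design section says of women who migrate for work: "these women could be lost to follow-up but the numbers are likely to be very small". No loss rate is given for women or children, and the sample size has no explicit allowance for loss.

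**The concern.** A participant lost to follow-up in this design has no post-baseline outcome at all, because there is only one follow-up visit. Including that participant therefore takes a method that either uses the baseline value in the model or supplies the missing outcome. The section makes the promise but names no such method, and two of its three analyses, as described, cannot keep it.

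Two things are at stake. The first is that the report would claim an analysis of all participants when the first-named primary analysis covers only women seen at 12 months. The second is that the analyst must choose how to reconcile the promise with the methods, possibly after the data are in, and different choices can give different estimates if loss is related to the score.

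**Working it through.** **Step 1. Set the promise against each analysis.**

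| Analysis as described | Woman or child with baseline only |
|---|---|
| t-test on cluster mean scores | Adds nothing to the 12-month group mean; omitted unless a value is imputed |
| Mixed linear regression of score | Omitted if only 12-month scores are the outcome; kept if both scores are modelled. The text does not say which |
| Random-effects logistic regression of CSOM prevalence | Adds nothing to 12-month prevalence; omitted unless a value is imputed |

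**Step 2. Reproduce the plan's own figure (Sample size calculation).** Inputs: 114 women per arm unclustered, about 20 per group, ICC 0.05. Design effect = 1 + (20 − 1) × 0.05 = 1.95, and 1.95 × 114 = 222.3, rounded up to the stated 223. The figure reproduces. No standard deviation is given, but 114 per arm at 80% power and 5% two-sided implies a standardised difference of √(2 × (1.96 + 0.8416)² / 114) = 0.371.

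**Step 3. Power if lost women are simply dropped at random.** With loss L (assumed, as none is stated), the group size becomes m = 20(1 − L). The effective number per arm is 15m / [1 + (m − 1) × 0.05], and power = Φ(0.371 × √(n_eff/2) − 1.96).

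| L (assumed) | Women lost of 600 | Effective n per arm | Power |
|---|---|---|---|
| 0 | 0 | 300/1.95 = 153.8 | 90.2% |
| 2% | 12 | 294/1.93 = 152.3 | 89.9% |
| 5% | 30 | 285/1.90 = 150.0 | 89.5% |
| 10% | 60 | 270/1.85 = 145.9 | 88.7% |
| 20% | 120 | 240/1.75 = 137.1 | 86.7% |
| 30% | 180 | 210/1.65 = 127.3 | 84.1% |

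Random loss is therefore not a serious threat to power.

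**Step 4. When completers mislead.** If an arm loses a fraction p, its completers' mean differs from its full mean by p × (mean of completers − mean of those lost). Suppose one arm only is affected and that gap is as large as the whole target effect, 0.371 SD (an assumption). The estimate then moves by 0.02 × 0.371 = 0.007 SD at 2% loss, 0.019 at 5%, 0.037 at 10% and 0.074 at 20%. With very small loss the shift is negligible.

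**Step 5. What modelling both scores does.** A simulation used 30 groups of 20, ICC 0.05, a true effect of 0.371 SD, and loss tied to the baseline score in the intervention arm only (an assumed, unfavourable pattern).

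| Overall loss | Completers, cluster comparison | Completers, 12-month mixed model | Mixed model of both scores |
|---|---|---|---|
| about 6% | 0.414 | 0.416 | 0.360 |
| about 12% | 0.423 | 0.426 | 0.373 |
| about 22% | 0.464 | 0.470 | 0.369 |

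The simulation standard error is about 0.008 for the two completer methods. The joint model rests on 30 runs per row, some with convergence warnings, so its column is indicative only. The pattern is still clear. A mixed model of 12-month scores alone shares the completers' shift, whereas the model that also uses baseline stays close to the truth and keeps all 600 women. The size of the shift depends on how strongly loss follows the baseline score, which the article cannot tell us.

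**The case against.** The strongest reply is that this is detail for the statistical analysis plan. The article sets two principles, that everyone is analysed and that missing data are not ignored, and the technique may be named elsewhere. That stands so far as it goes: an unnamed imputation method is not a finding in a condensed article. What remains is that the article makes a positive promise and then describes analyses that do not deliver it, with no link between the two.

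Several stronger readings are tempting and are not supported:

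- *None of the analyses can include those lost.* The mixed linear model is not restricted to 12-month scores. Fitted to both scores it keeps women with only a baseline value. Imputation could also feed the t-test and the logistic model.
- *The plan must either drop them or fill in ad hoc.* Joint modelling and multiple imputation are open to it. Carrying the baseline value forward is mentioned nowhere, so an effect shrunk by that method should not be charged to this plan.
- *Bias is to be expected.* The article describes the women as not generally mobile and backs this with a census count. That covers migration, not other reasons for loss, and it says nothing of children, but no text points to large or differential loss.
- *Children will be lost by leaving for school or by turning 13.* The sentence "Older children are increasingly moving to the district capital for the later years of high school, which would make followup assessment difficult" explains why 12 was chosen as the upper age. It describes a guard against loss. The age limit is an entry criterion, and nothing says that an enrolled child who turns 13 is not re-examined.

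**Conclusion.** The point holds in a limited form. The inclusion promise is not achievable by the cluster-level t-test or the CSOM logistic model as described, and the one listed analysis that could honour it for women is not stated to use the baseline score.

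The consequence is conditional. Under random loss, power stays above 84% even at an assumed 30% loss. Bias requires loss that is appreciable and related to outcome or unequal between arms. In the assumed unfavourable pattern at about 12% overall loss, completer analyses gave 0.42 to 0.43 SD against a true 0.371. The article's own expectation for migration points to far less loss than that.

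The change is still worth making. Baseline scores are being collected anyway, and using them adds precision as well as keeping women who miss the second visit.

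**What to change.** In the Statistical analysis section:

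1. Define intention-to-treat as analysis of participants in the arm to which their group was allocated, and state separately how missing 12-month outcomes are handled.
2. Specify the individual-level primary analysis as one mixed model of the baseline and 12-month scores, with random effects for group and for woman and a common baseline mean across arms. The effect is the arm difference at 12 months. Let the group effect differ between the two occasions, so that the standard error does not assume that differences between groups stay fixed over the year.
3. Describe the cluster-level t-test as using women with 12-month scores, or run it on imputed data.
4. For CSOM, use multilevel multiple imputation that includes group, arm, baseline CSOM and age, followed by the planned random-effects logistic model.
5. Report loss by arm and add a sensitivity analysis for departures from missing at random.

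The cost is wording and modest extra programming, with no new data. The main methods would rest on missing at random, which the data cannot confirm. Data collection has begun, so the choice should be fixed before any 12-month outcome is seen by arm.
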